Knowledge of danger signs during pregnancy has 14 items, Knowledge of danger signs of labor and childbirth has 9 items and knowledge of neonatal danger signs has 11 items. All Knowledge score will be computed by adding the total number of correct spontaneous responses to maximum number of items with a minimum score of 0 and maximum of number of items (0 when a mother mentioned none of the key danger signs and maximum number when the mother mentioned all the danger signs). Spontaneous response is respondents’ naming of danger signs without giving option of the respective signs. Accordingly, two categories will be developed for knowledge of danger signs (Good and poor categories). Women who mention at least three neonatal danger signs will be considered to have good knowledge whereas those who mentioned less than three of the danger signs will be labelled to have poor knowledge as stated by several studies. Questionnaire on BPCR is adopted and modified from monitoring BPCR tools for maternal and new-born health (Maternal, 2004). Attitude towards skilled delivery service utilization has 12 items that will be measured by using Likert scale where respondents are supposed to strongly agree, agree, neutral, disagree and strongly disagree. The overall attitude score will computed by summing up the items after performing the reverse scoring for negatively worded sentences. A higher composite score indicated a more favourable attitude.

*Perception of Pregnancy Risk Questionnaire (PPRQ****)*** was developed by Heaman and Gopton (Heaman and Gupton, 2009). It is a self-report questionnaire consisting of 9 visual analogue scales designed to measure a pregnant woman’s perception of her pregnancy risks. This questionnaire consists of two subscales that include four questions about the risk to self (mother), (for example “is a risk of having a cesarean section”); and five questions about risk to the baby, (for example “is a risk of baby having a birth defect”). “Respondents will be asked to put a vertical mark through the line to indicate their assessment of risk for each Item,” (yielding a score ranging from 0-100). A total PPRQ score will be obtained by adding the score for each of the 9 items, and then dividing by 9, to obtain a score out of 100. Higher scores will indicate higher levels of perceived risk.

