**Part VII General Self-Efficacy Scale**

|  | Not at  all true | Hardly  true | Moderately  true | Exactly  true |
| --- | --- | --- | --- | --- |
| 1. I can always manage to solve difficult problems if I try hard enough | □ | □ | □ | □ |
| 2. If someone opposes me, I can find the means and ways to get what I want. | □ | □ | □ | □ |
| 3. It is easy for me to stick to my  aims and accomplish my goals. | □ | □ | □ | □ |
| 4. I am confident that I could deal efficiently with unexpected events. | □ | □ | □ | □ |
| 5. Thanks to my resourcefulness, I know how to handle unforeseen situations. | □ | □ | □ | □ |
| 6. I can solve most problems if I invest the necessary effort. | □ | □ | □ | □ |
| 7. I can remain calm when facing difficulties because I can rely on my coping abilities. | □ | □ | □ | □ |
| 8. When I am confronted with a problem, I can usually find several solutions. | □ | □ | □ | □ |
| 9. If I am in trouble, I can usually think of a solution | □ | □ | □ | □ |
| 10. I can usually handle whatever comes my way. | □ | □ | □ | □ |

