| 813 | My religious leaders repeatedly notified us about new-born danger signs | 1. Strongly disagree; 2. Disagree; 3.Neutral; 4. Agree; 5. Strongly agree |  |
| 814 | My religious leaders reminded us to early seek healthcare when any danger signs occurred during pregnancy, labour and child birth, and new-born, post-partum period | 1. Strongly disagree; 2. Disagree; 3.Neutral; 4. Agree; 5. Strongly agree |  |
| 815 | My religious leaders commonly encouraged us to follow postnatal care services | 1. Strongly disagree; 2. Disagree; 3.Neutral; 4. Agree; 5. Strongly agree |  |
| 816 | My religious leaders commonly notified us on family planning and immunization of baby | 1. Strongly disagree; 2. Disagree; 3.Neutral; 4. Agree; 5. Strongly agree |  |
| 817 | My religious leaders commonly notified us on new-born care | 1. Strongly disagree; 2. Disagree; 3.Neutral; 4. Agree; 5. Strongly agree |  |
| **818** | My religious leaders commonly disseminated MCH messages on congregation | 1. Strongly disagree; 2. Disagree; 3.Neutral; 4. Agree; 5. Strongly agree |  |
| **819** | Religious provided support that is important to maternal and child health promotion | 1. Strongly disagree; 2. Disagree; 3.Neutral; 4. Agree; 5. Strongly agree |  |
| **820** | I feel helped by religious leaders during my pregnancy and child birth | 1. Strongly disagree; 2. Disagree; 3.Neutral; 4. Agree; 5. Strongly agree |  |
| **821** | I feel helped by religious leaders by encouraging to receive MCH care regularly during my pregnancy and child birth | 1. Strongly disagree; 2. Disagree; 3.Neutral; 4. Agree; 5. Strongly agree |  |
| **822** | I feel supported by religious leaders as they initiate to seek healthcare whenever any danger signs is present | 1. Strongly disagree; 2. Disagree; 3.Neutral; 4. Agree; 5. Strongly agree |  |
| **823** | I feel to have been offered support by religious leaders regarding MCH | 1. Strongly disagree; 2. Disagree; 3.Neutral; 4. Agree; 5. Strongly agree |  |
| **824** | I believe that religious leaders are knowledgeable about MCH | 1. Strongly disagree; 2. Disagree; 3.Neutral; 4. Agree; 5. Strongly agree |  |
| **825** | I perceive that religious leaders are welcomed by pregnant mothers as they transmit MCH messages  I believe that religious leaders are credible contributors to maternal and child health promotion | 1. Strongly disagree; 2. Disagree; 3.Neutral; 4. Agree; 5. Strongly agree |  |

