| **826** | I believe that religious leaders are trusted while teaching & giving information maternal and child health | 1. Strongly disagree; 2. Disagree; 3.Neutral; 4. Agree; 5. Strongly agree |  |
| **827** | I perceive that religious leaders were following whether or not maternal health services were utilized properly and intended | 1. Strongly disagree; 2. Disagree; 3.Neutral; 4. Agree; 5. Strongly agree |  |
| **828** | I perceived that religious leaders took responsibility to follow-up about regular MCH service utilization | 1. Strongly disagree; 2. Disagree; 3.Neutral; 4. Agree; 5. Strongly agree |  |
| **829** | I perceive that religious leaders felt accountable to monitor taking iron-folate drugs as prescribed | 1. Strongly disagree; 2. Disagree; 3.Neutral; 4. Agree; 5. Strongly agree |  |
| **830** | I am impressed and influenced watching my religious leader disseminating MCH messages | 1. Strongly disagree; 2. Disagree; 3.Neutral; 4. Agree; 5. Strongly agree |  |
| **831** | I am convinced to receive MCH care services regularly following what I saw from my religious leaders’ family | 1. Strongly disagree; 2. Disagree; 3.Neutral; 4. Agree; 5. Strongly agree |  |
| **832** | I feel religious leaders can be role model in seeking care when they have an illness | 1. Strongly disagree; 2. Disagree; 3.Neutral; 4. Agree; 5. Strongly agree |  |
| **833** | Religious leaders were observed mobilized by BCC materials to disseminate MCH messages | 1. Strongly disagree; 2. Disagree; 3.Neutral; 4. Agree; 5. Strongly agree |  |
| **834** | In our church/mosque religious leaders were mostly observed in that they kept promoting maternal and child health | 1. Strongly disagree; 2. Disagree; 3.Neutral; 4. Agree; 5. Strongly agree |  |
| **835** | Religious leaders were mostly observed in that they discourage harmful traditional practices related to pregnancy, Labor and Child Birth | 1. Strongly disagree; 2. Disagree; 3.Neutral; 4. Agree; 5. Strongly agree |  |

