**ክፍል VI የእርግዝና ስጋት ግንዛቤ**

1. በዚህ እርግዝና ወቅት ለራሴ ያለው አደጋ፡-

ምንም ስጋት የለም እጅግ በጣም ከፍተኛ ስጋት

1. በዚህ እርግዝና ወቅት የማኅፀን ልጅ ስጋት፡-

ምንም ስጋት የለም እጅግ በጣም ከፍተኛ ስጋት

1. በዚህ እርግዝና ወቅት የደም መፍሰስ ችግር (ብዙ ደም የማጣት) ስጋት፡-

ምንም ስጋት የለም እጅግ በጣም ከፍተኛ ስጋት

1. በቀዶ ሕክምና የመውለድ ዕድሌ፡-

ምንም ስጋት የለም እጅግ በጣም ከፍተኛ ስጋት

1. በዚህ እርግዝና ወቅት የመሞት ዕድሌ፡-

ምንም ስጋት የለም እጅግ በጣም ከፍተኛ ስጋት

1. ልጄ ያለጊዜው የመወለድ አደጋ፡-

ምንም ስጋት የለም እጅግ በጣም ከፍተኛ ስጋት

1. የልጄ የወሊድ ችግር ያለበት አደጋ፡-

ምንም ስጋት የለም እጅግ በጣም ከፍተኛ ስጋት

1. ልጄ ወደ አራስ ሕፃን ከፍተኛ እንክብካቤ ክፍል የመሄድ አደጋ የሚከተለው ነው፡-

ምንም ስጋት የለም እጅግ በጣም ከፍተኛ ስጋት

1. በዚህ እርግዝና ወቅት ልጄ የመሞት አደጋ፡-

እጅግ በጣም ከፍተኛ ስጋት እጅግ በጣም ከፍተኛ ስጋት

ክፍል VII ደህንነቱ የተጠበቀ የወሊድ አገልግሎት አጠቃቀም ላይ ያለ አመለካከት

| 701 | አንዳንድ ሰዎች ማንኛውም ነፍሰ ጡር ሴት የመውለድ ችግር ሊፈጠር ይችላል ብለው ያምናሉ | 1. በጣም አልስማማም, 2. አልስማማም, 3. ገለልተኛ, 4. እስማማለሁ, 5. በጣም እስማማለሁ |  |
| --- | --- | --- | --- |
| 702 | አንዳንድ ሰዎች የወሊድ ችግሮች ለሴት ጤንነት አደገኛ ሊሆኑ እንደሚችሉ ይሰማቸዋል | 1. በጣም አልስማማም, 2. አልስማማም, 3. ገለልተኛ, 4. እስማማለሁ, 5. በጣም እስማማለሁ |  |
| 703 | የወሊድ ችግሮች አዲስ ለተወለደ ሕፃን ጤና አደገኛ ሊሆኑ እንደማይችሉ ይታመናል | 1. በጣም አልስማማም, 2. አልስማማም, 3. ገለልተኛ, 4. እስማማለሁ, 5. በጣም እስማማለሁ |  |
| 706 | በአንዳንድ ሰዎች እምነት አንዲት ሴት ልጇን የምትወልድበትን ቦታ አስቀድመህ ማቀድ አለባት | 1. በጣም አልስማማም, 2. አልስማማም, 3. ገለልተኛ, 4. እስማማለሁ, 5. በጣም እስማማለሁ |  |
| 707 | አንዳንድ ሴቶች ወደሚወልዱበት ቦታ እንዴት እንደሚደርሱ አስቀድመው ማቀድ እንደሌለባቸው ይሰማቸዋል. | 1. በጣም አልስማማም, 2. አልስማማም, 3. ገለልተኛ, 4. እስማማለሁ, 5. በጣም እስማማለሁ |  |
| 708 | አንዳንድ ሴቶች እያንዳንዱ ነፍሰ ጡር ሴት የሰለጠነ የወሊድ እንክብካቤ እንደሚያስፈልገው ይሰማቸዋል | 1. በጣም አልስማማም, 2. አልስማማም, 3. ገለልተኛ, 4. እስማማለሁ, 5. በጣም እስማማለሁ |  |
| 709 | ጥቂት ሴቶች በወሊድ ጊዜ የወንድ ጤና ባለሙያዎች መገኘት ሥነ ምግባር የጎደለው እና አሳፋሪ እንደሆነ ይሰማቸዋል | 1. በጣም አልስማማም, 2. አልስማማም, 3. ገለልተኛ, 4. እስማማለሁ, 5. በጣም እስማማለሁ |  |
| 710 | እንደ አንዳንድ ነፍሰ ጡር እናቶች ስሜት በወሊድ ክፍል ውስጥ አልጋ ላይ መውለድ በጣም አሳፋሪ ነው. | 1. በጣም አልስማማም, 2. አልስማማም, 3. ገለልተኛ, 4. እስማማለሁ, 5. በጣም እስማማለሁ |  |
| 711 | ብዙ ሴቶች ሴቶች ለመውለድ ወደ ጤና ተቋም አይሄዱም ብለው ያምናሉ፣ ይህም በዋነኝነት በጣም ውድ ስለሆነ ነው። | 1. በጣም አልስማማም, 2. አልስማማም, 3. ገለልተኛ, 4. እስማማለሁ, 5. በጣም እስማማለሁ |  |
| 712 | ብዙ ሴቶች ሴቶች ለመውለድ ወደ ጤና ተቋም የማይሄዱት የጤና ባለሙያዎች በአክብሮት ስለማያዩአቸው እንደሆነ ያምናሉ  . | 1. በጣም አልስማማም, 2. አልስማማም, 3. ገለልተኛ, 4. እስማማለሁ, 5. በጣም እስማማለሁ |  |

ክፍል VIII የሃይማኖት መሪዎች የተሳትፎ ልኬት መለኪያ መሣሪያ

| 801 | በቀጠሮ ወይም በቀጠሮ ላይ ተመስርቼ የቅድመ ወሊድ ክትትል እንዳደርግ የሃይማኖት መሪዬ የማያቋርጥ ማሳሰቢያ ነበር። | 1. በጣም አልስማማም, 2. አልስማማም, 3. ገለልተኛ, 4. እስማማለሁ, 5. በጣም እስማማለሁ |  |
| --- | --- | --- | --- |
| 802 | የሀይማኖት መሪዎቼ ብረት ፎሌት ያለማቋረጥ መውሰድ እንዲጨርሱ ደጋግመው ያሳስባሉ | 1. በጣም አልስማማም, 2. አልስማማም, 3. ገለልተኛ, 4. እስማማለሁ, 5. በጣም እስማማለሁ |  |

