| 803 | የሃይማኖት መሪዎቼ ስለ ቴታነስ ቶክሳይድ ክትባት ደጋግመው አሳውቀውናል። | 1. በጣም አልስማማም, 2. አልስማማም, 3. ገለልተኛ, 4. እስማማለሁ, 5. በጣም እስማማለሁ |  |
| 804 | የሃይማኖት መሪዎቼ ስለ ግብረ ሥጋ ግንኙነት የሚተላለፉ በሽታዎች እና ስለ ኤችአይቪ ምርመራ እና ምክር ደጋግመው አሳውቀውናል። | 1. በጣም አልስማማም, 2. አልስማማም, 3. ገለልተኛ, 4. እስማማለሁ, 5. በጣም እስማማለሁ |  |
| 805 | የሃይማኖት መሪዎቼ የሰለጠነ የወሊድ አገልግሎትን እንድንለይ ገፋፍተውናል። | 1. በጣም አልስማማም, 2. አልስማማም, 3. ገለልተኛ, 4. እስማማለሁ, 5. በጣም እስማማለሁ |  |
| 806 | የሃይማኖት መሪዎቼ በጤና ተቋም እንድንወልድ ያበረታቱናል። | 1. በጣም አልስማማም, 2. አልስማማም, 3. ገለልተኛ, 4. እስማማለሁ, 5. በጣም እስማማለሁ |  |
| 807 | የሃይማኖት መሪዎቼ በምጥ ጊዜ መጓጓዣ እንድናዘጋጅ ያበረታቱናል። | 1. በጣም አልስማማም, 2. አልስማማም, 3. ገለልተኛ, 4. እስማማለሁ, 5. በጣም እስማማለሁ |  |
| 808 | የሃይማኖት መሪዎቼ በወሊድ ጊዜ እና በድህረ ወሊድ ወቅት ለእኔ እና ለቤተሰቤ የድጋፍ ምንጮችን እንድንለይ በተለምዶ ያበረታቱናል። | 1. በጣም አልስማማም, 2. አልስማማም, 3. ገለልተኛ, 4. እስማማለሁ, 5. በጣም እስማማለሁ |  |
| 809 | የሃይማኖት መሪዎቼ ከወሊድ ጋር የተያያዙ ተጨማሪ ወጪዎችን እንድናዘጋጅ፣ ለእኔ እንክብካቤ እና አዲስ ለተወለደው ልጄ እንክብካቤ የሚያስፈልጉትን ነገሮች እንድናዘጋጅ በተለምዶ ያበረታቱናል። | 1. በጣም አልስማማም, 2. አልስማማም, 3. ገለልተኛ, 4. እስማማለሁ, 5. በጣም እስማማለሁ |  |
| 810 | የሃይማኖት መሪዎቼ በእርግዝና ወቅት ስለ አደገኛ ምልክቶች ደጋግመው አሳውቀውናል። | 1. በጣም አልስማማም, 2. አልስማማም, 3. ገለልተኛ, 4. እስማማለሁ, 5. በጣም እስማማለሁ |  |
| 811 | የሃይማኖት መሪዎቼ በምጥ እና ልጅ በሚወልዱበት ወቅት ስለ አደገኛ ምልክቶች ደጋግመው አሳውቀውናል። | 1. በጣም አልስማማም, 2. አልስማማም, 3. ገለልተኛ, 4. እስማማለሁ, 5. በጣም እስማማለሁ |  |
| 812 | የሃይማኖት መሪዎቼ ከወሊድ በኋላ ባሉት ጊዜያት ስለ አደገኛ ምልክቶች ደጋግመው አሳውቀውናል። | 1. በጣም አልስማማም, 2. አልስማማም, 3. ገለልተኛ, 4. እስማማለሁ, 5. በጣም እስማማለሁ |  |
| 813 | የሃይማኖት መሪዎቼ አዲስ ስለተወለዱ የአደጋ ምልክቶች ደጋግመው አሳውቀውናል። | 1. በጣም አልስማማም, 2. አልስማማም, 3. ገለልተኛ, 4. እስማማለሁ, 5. በጣም እስማማለሁ |  |
| 814 | የሃይማኖት መሪዎቼ በእርግዝና ወቅት፣ ምጥ እና ልጅ በሚወልዱበት ወቅት፣ እና አዲስ በተወለደ፣ ከወሊድ በኋላ በሚከሰት ጊዜ ማንኛውም የአደጋ ምልክቶች ሲከሰቱ ጤናን ቀድመን እንድንፈልግ አስታውሰውናል። | 1. በጣም አልስማማም, 2. አልስማማም, 3. ገለልተኛ, 4. እስማማለሁ, 5. በጣም እስማማለሁ |  |
| 815 | የሀይማኖት መሪዎቼ የድህረ ወሊድ አገልግሎት እንድንከተል ያበረታቱናል። | 1. በጣም አልስማማም, 2. አልስማማም, 3. ገለልተኛ, 4. እስማማለሁ, 5. በጣም እስማማለሁ |  |
| 816 | የኃይማኖት መሪዎቼ ስለ ቤተሰብ ምጣኔ እና ስለ ሕፃን ክትባቶች በተለምዶ ያሳውቁን ነበር። | 1. በጣም አልስማማም, 2. አልስማማም, 3. ገለልተኛ, 4. እስማማለሁ, 5. በጣም እስማማለሁ |  |
| 817 | የሃይማኖት መሪዎቼ አዲስ ስለተወለደው እንክብካቤ ብዙ ጊዜ ያሳውቁን ነበር። | 1. በጣም አልስማማም, 2. አልስማማም, 3. ገለልተኛ, 4. እስማማለሁ, 5. በጣም እስማማለሁ |  |
| **818** | የሀይማኖት መሪዎቼ የእናቶች እና የህፃናት ጤና መልእክቶችን በጉባኤው ላይ ያሰራጫሉ። | 1. በጣም አልስማማም, 2. አልስማማም, 3. ገለልተኛ, 4. እስማማለሁ, 5. በጣም እስማማለሁ |  |
| **819** | የሃይማኖት አባቶች ለእናቶች እና ህጻናት ጤና እድገት ጠቃሚ የሆነ ድጋፍ ይሰጣሉ | 1. በጣም አልስማማም, 2. አልስማማም, 3. ገለልተኛ, 4. እስማማለሁ, 5. በጣም እስማማለሁ |  |
| **820** | በእርግዝና እና ልጅ በምወለድበት ጊዜ የሃይማኖት መሪዎች እንደረዱኝ ይሰማኛል | 1. በጣም አልስማማም, 2. አልስማማም, 3. ገለልተኛ, 4. እስማማለሁ, 5. በጣም እስማማለሁ |  |

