| **821** | በእርግዝና እና በወሊድ ጊዜ የእናቶች እና የህፃናት ጤና አጠባበቅ እንድገኝ በማበረታታት የሃይማኖት መሪዎች እንደረዱኝ ይሰማኛል። | 1. በጣም አልስማማም, 2. አልስማማም, 3. ገለልተኛ, 4. እስማማለሁ, 5. በጣም እስማማለሁ |  |
| **822** | የአደጋ ምልክቶች በሚታዩበት ጊዜ ሁሉ የጤና እንክብካቤ ለመፈለግ ሲነሱ የሃይማኖት መሪዎች ድጋፍ እንደሚሰጡኝ ይሰማኛል። | 1. በጣም አልስማማም, 2. አልስማማም, 3. ገለልተኛ, 4. እስማማለሁ, 5. በጣም እስማማለሁ |  |
| **823** | የእናቶች እና ህፃናት ጤናን በተመለከተ ከሀይማኖት አባቶች ድጋፍ እንደተደረገልኝ ይሰማኛል። | 1. በጣም አልስማማም, 2. አልስማማም, 3. ገለልተኛ, 4. እስማማለሁ, 5. በጣም እስማማለሁ |  |
| **824** | የሃይማኖት መሪዎች ስለ እናቶች እና ህፃናት ጤና ጠንቅቀው ያውቃሉ ብዬ አምናለሁ። | 1. በጣም አልስማማም, 2. አልስማማም, 3. ገለልተኛ, 4. እስማማለሁ, 5. በጣም እስማማለሁ |  |
| **825** | የሃይማኖት መሪዎች የእናቶች እና የህፃናት ጤና መልዕክቶችን ሲያስተላልፉ ነፍሰ ጡር እናቶች እንደሚቀበሏቸው ተረድቻለሁ | 1. በጣም አልስማማም, 2. አልስማማም, 3. ገለልተኛ, 4. እስማማለሁ, 5. በጣም እስማማለሁ |  |
| **826** | የሃይማኖት መሪዎች ለእናቶች እና ህጻናት ጤና እድገት ታማኝ አስተዋፅዖ አበርክተዋል ብዬ አምናለሁ። | 1. በጣም አልስማማም, 2. አልስማማም, 3. ገለልተኛ, 4. እስማማለሁ, 5. በጣም እስማማለሁ |  |
| **827** | የሃይማኖት መሪዎች ስለ እናቶች እና ህፃናት ጤና ሲያስተምሩ እና ሲሰጡ ይታመናሉ ብዬ አምናለሁ። | 1. በጣም አልስማማም, 2. አልስማማም, 3. ገለልተኛ, 4. እስማማለሁ, 5. በጣም እስማማለሁ |  |
| **828** | የእናቶች ጤና አገልግሎት በአግባቡ ጥቅም ላይ መዋሉን እና አለመሆኑን የሀይማኖት መሪዎች እየተከታተሉት እንደሆነ እገነዘባለሁ። | 1. በጣም አልስማማም, 2. አልስማማም, 3. ገለልተኛ, 4. እስማማለሁ, 5. በጣም እስማማለሁ |  |
| **829** | የሃይማኖት መሪዎች ስለ መደበኛ የእናቶች እና ህጻናት ጤና አገልግሎት አጠቃቀምን የመከታተል ሃላፊነት እንደሚወስዱ ተረድቻለሁ | 1. በጣም አልስማማም, 2. አልስማማም, 3. ገለልተኛ, 4. እስማማለሁ, 5. በጣም እስማማለሁ |  |
| **830** | የሃይማኖት መሪዎች በታዘዘው መሠረት የብረት-ፎሌት መድኃኒቶችን የመቆጣጠር ኃላፊነት እንዳለባቸው እንደሚሰማቸው ተገንዝቤያለሁ | 1. በጣም አልስማማም, 2. አልስማማም, 3. ገለልተኛ, 4. እስማማለሁ, 5. በጣም እስማማለሁ |  |
| **831** | የሀይማኖት መሪዬ የእናቶች እና የህፃናት ጤና መልእክቶችን ሲያሰራጭ በመመልከቴ ተደንቄያለሁ እና ተጽኖአለሁ። | 1. በጣም አልስማማም, 2. አልስማማም, 3. ገለልተኛ, 4. እስማማለሁ, 5. በጣም እስማማለሁ |  |
| **832** | ከሀይማኖት መሪዎቼ ቤተሰብ ያየሁትን በመከተል የእናቶች እና የህፃናት ጤና አጠባበቅ አገልግሎቶችን በመደበኛነት እንደማገኝ እርግጠኛ ነኝ | 1. በጣም አልስማማም, 2. አልስማማም, 3. ገለልተኛ, 4. እስማማለሁ, 5. በጣም እስማማለሁ |  |
| **833** | የሃይማኖት መሪዎች በህመም ጊዜ እንክብካቤን በመፈለግ ረገድ አርአያ ሊሆኑ እንደሚችሉ ይሰማኛል። | 1. በጣም አልስማማም, 2. አልስማማም, 3. ገለልተኛ, 4. እስማማለሁ, 5. በጣም እስማማለሁ |  |
| **834** | የእናቶችና ህጻናት ጤና መልእክቶችን ሲያሰራጩ የሃይማኖት አባቶች ተስተውለዋል። | 1. በጣም አልስማማም, 2. አልስማማም, 3. ገለልተኛ, 4. እስማማለሁ, 5. በጣም እስማማለሁ |  |
| **835** | በቤተ ክርስቲያናችን/መስጊድ የሀይማኖት አባቶች የእናቶችንና የህፃናትን ጤና በማስተዋወቅ ረገድ ባብዛኛው ይስተዋላል | 1. በጣም አልስማማም, 2. አልስማማም, 3. ገለልተኛ, 4. እስማማለሁ, 5. በጣም እስማማለሁ |  |
| **836** | የሃይማኖት አባቶች ከእርግዝና፣ ምጥ እና ልጅ መውለድ ጋር የተያያዙ ጎጂ ልማዳዊ ድርጊቶችን እንደሚያበረታቱ በመግለጽ ይስተዋላል | 1. በጣም አልስማማም, 2. አልስማማም, 3. ገለልተኛ, 4. እስማማለሁ, 5. በጣም እስማማለሁ |  |

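### The annexed Amharic questionnaire reverses one engagement item, loses the low anchor of one of nine risk items, numbers the engagement list differently from item 826 on, and omits the self-efficacy scale

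*Protocol*

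**What the plan says.** Objective 4 is to develop and validate a scale of religious leaders' engagement, and the study design summary table names exploratory factor analysis as its method. The items are in Annex 1, Part IX, which is marked for end-line use, and in the corresponding engagement part of the Amharic version (Annex 2, Part VIII).

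- **Last engagement item.** English 835: "Religious leaders were mostly observed in that they discourage harmful traditional practices related to pregnancy, Labor and Child Birth". Amharic 836: "ጎጂ ልማዳዊ ድርጊቶችን እንደሚያበረታቱ በመግለጽ ይስተዋላል".
- **Row 825.** The English row holds a statement about leaders being welcomed and then a second statement, "I believe that religious leaders are credible contributors to maternal and child health promotion", with a single set of answers. In Amharic the second statement is item 826: "የሃይማኖት መሪዎች ለእናቶች እና ህጻናት ጤና እድገት ታማኝ አስተዋፅዖ አበርክተዋል ብዬ አምናለሁ".
- **Pregnancy risk, item 9.** The English anchors run from no risk to extremely high risk. The Amharic anchors are "እጅግ በጣም ከፍተኛ ስጋት እጅግ በጣም ከፍተኛ ስጋት". Section 4.16 says: "A total PPRQ score will be obtained by adding the score for each of the 9 items", divided by 9, with each item marked on a 0-100 line.
- **Self-efficacy.** Section 4.7 lists it as a behavioural variable and Annex 1 contains "Part VII General Self-Efficacy Scale". In the Amharic form Part VII is the attitude scale, and no self-efficacy part appears.

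Section 4.18 describes translation into Amharic with blinded back-translation, followed by a pilot and pre-test. Section 4.17 recruits Hadiyisa-speaking data collectors. The Hadiyisa annex holds only the key messages.

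**The concern.** In Objective 4 the item wording is itself the product being validated. If the Amharic form is used as annexed, a woman who sees her leader opposing harmful practices would have to disagree with item 836. That answer would then count against engagement unless someone noticed. No reverse scoring is stated for this scale; section 4.16 states it only for the attitude scale. Because the scale is marked for end-line, a baseline round would not expose the error.

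The risk total includes a line whose low end has no meaning as printed. Two numberings for one scale invite wrong labels when answers are coded or reported. A variable on the list would have no data if only the Amharic form were used.

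**Working it through.** There is no figure in the plan to reproduce, so the check compares the two forms item by item and then bounds the effect of each difference.

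**1. Direction of the last engagement item.** The document itself shows what the Amharic verb means. English 806 says that leaders encouraged the women to give birth at a health facility, and Amharic 806 renders this as "የሃይማኖት መሪዎቼ በጤና ተቋም እንድንወልድ ያበረታቱናል". The verb in Amharic 836 has the same stem. So 836 asks about encouraging harmful practices, where English 835 asks about discouraging them. Reversed statements: 1 of 36.

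**2. Numbering.** Items 801 to 824 correspond. After that:

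| Content | English | Amharic |
|---|---|---|
| Welcomed by mothers | 825 (first half) | 825 |
| Credible contributors | 825 (second half) | 826 |
| Trusted | 826 | 827 |
| Accountable for iron-folate | 829 | 830 |
| Harmful practices | 835 | 836 |

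Each English number from 826 to 835 equals the Amharic number minus 1. Ten numbers (835 − 826 + 1 = 10) therefore carry different content. Counted by statement, eleven move: the second half of 825 plus the ten rows 826 to 835. One of the eleven is the reversed item. English has 35 rows holding 36 statements; Amharic has 36 rows.

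**3. Risk total.** Score = (sum of 9 items)/9, each item 0-100. Items 1 to 8 in Amharic carry a no-risk low anchor; item 9 does not. The largest possible effect of item 9 is 100/9 = 11.1 points, reached only if its mark moves across the whole line.

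**4. Effect on the engagement scale (illustration).** The documents give neither loadings nor a scoring rule. Assume one factor, k = 36 items and equal loadings λ, so items correlate λ². Cronbach's alpha = [k/(k − 1)] × (1 − k/S), where S is the sum of the correlation matrix.

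- All items aligned: S = 36 + 36 × 35 × λ². At λ = 0.6, S = 489.6 and alpha = (36/35)(1 − 36/489.6) = 0.953.
- One item reversed and not recoded: S = 36 + (34² − 36) × λ². At λ = 0.6, S = 439.2 and alpha = 0.944.
- At λ = 0.4 alpha goes from 0.873 to 0.857; at λ = 0.8 from 0.985 to 0.979.

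If the items were simply summed, a fully reversed answer on a 1-5 item would cost 4 points out of a range of 36 × 4 = 144, or 2.8%.

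**5. Self-efficacy.** The English parts run VI risk, VII self-efficacy, VIII attitude, IX engagement. The Amharic parts run VI risk, VII attitude, VIII engagement. All 10 self-efficacy items are missing.

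**The case against.** A reader might infer that the engagement scale and the risk score rest on different questions from those defined. They do not: 35 of 36 engagement statements correspond, and risk item 9 asks the same question in both languages with one wrong label. After eight lines running in the same direction, many women would probably mark the ninth the same way.

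A reader might also infer that ten items will be mislabelled and the factors misnamed. That happens only if Amharic answers are coded against the English numbers, and nothing in the protocol says so; the item list in the electronic data-capture application is not shown. The Amharic split in fact repairs a double-barrelled English row.

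It is tempting to call the Amharic version the form used in the field. The protocol does not state the language of interview, and the recruitment of Hadiyisa speakers leaves this open. What can be said is that it is the only translated questionnaire annexed.

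The planned pre-test covers wording and allows changes, and a reversed item would be expected to load with the opposite sign in the factor analysis, where it could be seen. On self-efficacy, the list of questionnaire sections in 4.16 and the analysis section do not mention it, so no stated analysis is lost.

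These points narrow the finding but do not remove it. A pre-test may catch the errors, but the described translation and back-translation left them in the annexed form.

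**Conclusion.** The four differences are in the text and should be corrected before the form is used. One of 36 engagement statements is reversed; one of nine risk items lacks its low anchor, with a bound of 11.1 points on the total; ten engagement numbers differ in content between the forms; and one listed variable has no Amharic items.

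The illustrated loss of reliability is small, and it rests on assumed loadings. The practical effects depend on the Amharic form being used as annexed and, for the numbering, on answers being coded by the English numbers.

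The point concerns Objective 4 and the secondary behavioural measures. It would be wrong to carry it over to Objectives 1 to 3: skilled delivery, antenatal care, danger-sign knowledge and the sample size do not depend on these items.

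**What to change.** Before use:

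- Correct Amharic 836 so that it says *discourage*.
- Set the low anchor of Amharic risk item 9 to *no risk at all*.
- Split English row 825 so that both forms share one 36-item list and one numbering, and use that list in the data dictionary.
- Add the self-efficacy scale to the Amharic form, or remove self-efficacy from the variable list.
- State the language in which the questionnaire is administered.

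If data were already collected on this form:

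- Drop item 836 rather than reverse-score it, because not encouraging a practice is not the same as discouraging it.
- Match items by content, not by number.
- Compute the risk score as the mean of items 1 to 8, dividing by 8. Keeping the divisor of 9 would shrink every score to 8/9 (88.9%) of its proper value.

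The cost is a revised form and data dictionary, with no extra participants or visits.

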# Annex 2 Amharic Version

የመጠይቁ መለያ ቁጥር
ቀበሌ

የቤት ቁጥር

የጠያቂ ስምና ፊርማ

ክፍል አንድ፡- ማህበረ-ዲሞክራሲያዊ ምላሽ ሰጪ ባህሪያት

| **Sir. No.** | **ጥያቄዎች** | **ምላሾች** | **Skip to** |
| --- | --- | --- | --- |
| 101 | ሙሉ ዕድሜ ዓመት |  |  |
| 102 | ዘርህ የቱ ነው? | 1. 1.ሀዲያ2.ጉራጌ3.ከምባታ4.ስልጤ5.ሌላ ይግለጹ |  |
| 103 | ሃይማኖትህ ምንድን ነው? | 1. 1.ፕሮቴስታንት2.ኦርቶዶክስ3.ሙስሊም4.ካቶሊክ5.ሌላ ይግለጹ። |  |
| 104 | የገቢ ምንጭ | --------- |  |
| 105 | ወርሃዊ ገቢ | --------Birr |  |
| 106 | ከጤና ጣቢያ አማካኝ ርቀት | በሜትር ------------- |  |
| 107 | ከሆስፒታል አማካይ ርቀት | በሜትር ------------- |  |
|  | ለእናቶች ጤና አገልግሎት ከፍለዋል? | 1. 1.አዎ2.አይ |  |
| 108 | ያገኙት ከፍተኛ የትምህርት ደረጃ ስንት ነው? | 1. መሃይም 2. ማንበብና መጻፍ ብቻ (መደበኛ ትምህርት የለም) 3. ክፍል 1-4 4. 5-8. 5. 9-10 6. 11 - 12 ክፍል 7. ከ12ኛ ክፍል በላይ |  |
| 109 | ሥራህ ምንድን ነው? | 1. የቤት እመቤት 2. ገበሬ 3. የመንግስት ሰራተኛ 4. ነጋዴ 5. የቤት ሰራተኛ 6.ሌላ (ይግለጹ)) |  |
| 110 | የጋብቻ ሁኔታዎ ምን ያህል ነው? | 1. በጭራሽ አላገባም  2. ያገባ  3.የተፋታ  4.የተለየ  5.የሞተባት  6.ሌላ (ይግለጹ) |  |
| 111 | የባልሽ ዕድሜ ሙሉ ዓመታት |  |  |
| 112 | የባልሽ ስራ | 1. የመንግስት ሰራተኛ 2. ነጋዴ 3.ገበሬ 4.ሌላ (ይግለዥ) |  |
| 113 | የባልሽ የትምህርት ደረጃ | 1. መሃይም 2. ማንበብና መጻፍ ብቻ (መደበኛ ትምህርት የለም) 3. ክፍል 1-4 4. 5-8. 5. 9-10 6. 11 - 12 ክፍል 7. ከ12ኛ ክፍል በላይ |  |
| 114 | የቤተሰብ መጠን |  |  |

ክፍል II፡ reproductive ምላሽ ሰጪ ታሪክ

| **Sir. No.** | **ጥያቄዎች** | **ምላሾች** | **Skip to** |
| --- | --- | --- | --- |
| **201** | ስንት ወር ነፍሰ ጡር ነህ?የተጠናቀቁ ወራት ብዛት ይመዝግቡ |  |  |
| **202** | ይህ የመጀመሪያ እርግዝናዎ ነው? |  |  |
| **203** | የእርግዝና ብዛት |  |  |
| **204** | በመጀመሪያው እርግዝናዎ ዕድሜዎ ስንት ነበር? | 1. ________ ዓመቶች 2. **አላስታውስም** |  |
| **205** | በህይወት የተወለዱ ልጆች ቁጥር | ሴት____ ወንድ ______ |  |
| **206** | ገና የተወለዱ ሰዎች ቁጥር | ሴት____ ወንድ ______ |  |
| **207** | የፅንስ ማስወረድ ቁጥር |  |  |
| **208** | ከነሱ ውስጥ ስንቶቹ በቤት ውስጥ ተወለዱ? | 1. የቀጥታ የልደት ቁጥር ______  2. አሁንም የልደት ቁጥር ____ |  |
| **209** | ስንቶቹ በጤና ተቋም ተወለዱ? | 1. የቀጥታ የልደት ቁጥር ______  2. አሁንም የልደት ቁጥር ____ |  |
| **210** | የአራስ ሞት አጋጥሞዎታል (ዕድሜ ከሰባት ቀን በታች)? | 1. አዎ  2. No  3. አላስታውስም። |  |
| **211** | ለ Q 210 አዎ ከሆነ ስንት ጊዜ? |  |  |
| **212** | ለ Q 210 አዎ ከሆነ , አዲስ የተወለደው ሕፃን የት ነው የተወለደው? | 1. ቤት  2. የጤና ተቋም  3. ሌላ (ይግለጹ)___________ |  |
| **213** | ባለፉት አምስት ዓመታት ውስጥ ስንት ጊዜ ልጅ ወለዱ? |  |  |
| **214** | የመጨረሻ ልጅህ መቼ ነው የተወለደው? | ___________/_________  Month year |  |
| **215** | በትውልድ ቅደም ተከተልዎ ውስጥ የመጨረሻው ልጅ የት ነው ያለው? |  |  |

ክፍል III የእናቶች ጤና አገልግሎት አጠቃቀም

| **Sir. No.** | **ጥያቄዎች** | **ምላሾች** | **Skip to** |
| --- | --- | --- | --- |
| 301 | የአሁኑ እርግዝናዎ የታቀደ ነው? | 1. አዎ 2. አይደለም |  |
| 302 | የመጨረሻ እርግዝናዎን ሲያውቁ ምን ስሜት ነበር | 1. ደስታ 2. ሀዘን 3. ምንም 4. ሌላ (ይግለጹ)_____ |  |
| 303 | በዚህ እርግዝና ውስጥ የጤና ችግር አጋጥሞዎታል? | 1. አዎ 2. አይደለም |  |
| 304 | ለ Q 303 አዎ ከሆነ, ምን ነበሩ? (*ምርጫዎቹን አታንብብ*) | 1. የሴት ብልት ደም መፍሰስ  2. የጭንቅላት ሕመምን ያስወግዱ  3. የፊት / የእጅ እብጠት  4. የማያቋርጥ ትውከት  5. የደም ግፊት መጨመር  6. ሌላ (ይግለጹ)_______________ |  |
| 305 | በዚህ እርግዝና ወቅት የጤና ተቋምን ጎበኙ? | 1. አዎ 2. አይደለም |  |
| 306 | ለ Q 305 አዎ ከሆነ, የመጎብኘት ምክንያት | 1. ከእርግዝና ጋር የተያያዘ የጤና ችግር  2. ከእርግዝና ጋር ያልተያያዙ የጤና ችግሮች  3. ለቅድመ ወሊድ እንክብካቤ  4. ሌላ (ይግለጹ) ------------------- |  |
| 307 | በዚህ እርግዝና ውስጥ ምንም አይነት የቅድመ ወሊድ እንክብካቤ አግኝተዋል? | 1. አዎ 2. አይደለም |  |
| 308 | በቅድመ ወሊድ እንክብካቤ ካልተከታተልክ ምክንያቶቹን ንገረኝ? **(ምርጫውን አታንብብ)** | 1. ስለ ቅድመ ወሊድ እንክብካቤ ምንም ወይም ትንሽ እውቀት  2. ምንም የጤና ችግር አጋጥሞታል  3. የጤና ተቋም ከቤቴ በጣም የራቀ ነው  4. ለቅድመ ወሊድ እንክብካቤ የሚወጣው ወጪ ተመጣጣኝ አይደለም  5. ለአገልግሎት ረጅም የጥበቃ ጊዜ  6. በጤና እንክብካቤ አቅራቢዎች ደካማ አያያዝ  7. የመጓጓዣ እጥረት  8. ወደ ጤና ተቋም ለመሄድ ጊዜ ማጣት  9. ሌላ (ይግለጹ) ------------------ |  |
| 309 | ለ Q 305, የመጎብኘት ምክንያት ለቅድመ ወሊድ እንክብካቤ ከሆነ, በየትኛው የእርግዝና እድሜ ላይ የእርግዝና ምርመራ ማድረግ ጀመሩ? | 1. ከአንድ እስከ ሶስት ወር  2. ከአራት እስከ ስድስት ወር  3. ከሰባት እስከ ዘጠኝ ወራት  4. አላስታውስም |  |
| 310 | ለእርግዝና ምርመራ ስንት ጊዜ ሄዱ? | 1. አንድ ጊዜ  2. ሁለት ጊዜ  3. ሦስት ጊዜ  4. ከሶስት እጥፍ በላይ  5. አላስታውስም |  |
| 311 | ለቅድመ ወሊድ አገልግሎት ወደ የትኛው ተቋም ሄዱ? | 1. ሆስፒታል 2. ጤና ጣቢያ  3. ጤና ጣቢያ 4. ሌላ (ይግለጹ)) ________________ |  |
| 312 | ይህንን ተቋም ለምን መረጡት? | 1. ወደ ቤቴ ቅርብ 2. ብቃት ያለው የጤና ሰራተኛ 3. ትክክለኛ ዋጋ፣ ሌላ (ይግለጹ)_________ |  |
| 313 | በእያንዳንዱ ጉብኝት የጤና ትምህርት ተሰጥቷል? | 1. አዎ ሁሌም 2. አዎ አንዳንዴ 3. በፍፁም 4. አታስታውስም። |  |
| 314 | ለ Q 313 አዎ ከሆነ, ከእርግዝና ጋር የተያያዙ አደገኛ ምልክቶችን ይነግሩዎታል | 1.አዎ 2. አይ 3. አላስታውስም |  |
| 315 | ለ Q 314 አዎ ከሆነ, ስለ የትኞቹ የአደጋ ምልክቶች ተነግሯችኋል? (ምርጫዎቹን አታንብብ) | 1. የሴት ብልት ደም መፍሰስ  2. የጭንቅላት ህመም  3. የፊት/የእጅ እብጠት  4. የማያቋርጥ ትውከት  5. የደም ግፊት  6. ሌላ (ይግለጹ)_ ________________ |  |
| 316 | ልጅዎን የት እንደሚወልዱ ተነግሮዎታል? | 1. አዎ 2. አይደለም |  |
| 317 | ለ Q 316 አዎ ከሆነ, የት ለመውለድ ተመክረዋል? | 1. ቤት 2. የጤና ተቋም 3. ሌላ (ይግለጹ)_________________ |  |
| 318 | በወሊድ ጊዜ ማን መገኘት እንዳለበት ተነግሮታል? | 1. አዎ 2. አይደለም |  |
| 319 | ለ Q 316 አዎ ከሆነ, በወሊድዎ ላይ እንዲገኝ የተመከረው ማን ነው? | 1. የሰለጠነ ባህላዊ ወሊድ 2. ዘመድ 3. የጤና ባለሙያ 4. ሌላ (ይግለጹ) |  |
| 320 | የማድረሻ ቀንዎ በፊት የሚከተሉትን ዕቃዎች እንዲያዘጋጁ ተነግሮዎታል | 1. ትራንስፖርት 2. ገንዘብ መቆጠብ 3. ደም ለጋሾችን መለየት 4. ምንም |  |
| 321 | ቴታነስ እንዳንያዝክ ክንድ ላይ መርፌ ተሰጥተሃል (ለቲታነስ የአካባቢ ጊዜን ተጠቀም)? | 1. አዎ 2. አይደለም |  |
| 322 | ለ Q 321አዎ ከሆነ, ስንት ጊዜ? |  |  |
| 323 | ካርዱ አለህ? (ከካርድ መመዝገቢያ ቀን ጀምሮ) | 1. TT1 ____/____/________  ቀን ወር አመት  2. TT2 ____/____/________  ቀን ወር አመት  3. TT3 ____/____/________  ቀን ወር አመት  4. TT4 ____/____/________  ቀን ወር አመት  5. TT5 ____/____/________  ቀን ወር አመት |  |
| 324 | የመጨረሻ ልጅህን የት ነው የወለድከው? | 1. ቤት  2. ሆስፒታል  3. ጤና ጣቢያ  4. ጤና ጣቢያ ሌላ ይግለጹ_________ |  |
| 325 | በእርግዝና ወቅት አጨስ ወይም ለሁለተኛ እጅ ማጨስ ተጋልጧል? | 1. አዎ 2. አይደለም |  |
| 326 | በእርግዝና ወቅት ለፀረ-ተባይ ወይም ለሌሎች መርዛማ ኬሚካሎች ተጋልጠዋል? | 1. አዎ 2. አይደለም |  |
| 327 | በእርግዝና ወቅት ለኤክስሬይ ወይም ለሌሎች ለሕክምና ያልሆኑ ራዲዮሎጂካል ንጥረ ነገሮች ተጋልጠዋል? | 1. አዎ 2. አይደለም |  |
| 328 | በእርግዝና ወቅት ፎሊክ አሲድ ወስደዋል? | 1. አዎ 2. አይደለም |  |
| 329 | በእርግዝና ወቅት አልኮል ጠጥተዋል? | 1. አዎ 2. አይደለም |  |

ክፍል IV የልደት ዝግጁነት እና ውስብስብነት ዝግጁነት

| **Sir. No.** | **ጥያቄዎች** | **ምላሾች** | **Skip to** |
| --- | --- | --- | --- |
| 401 | "የልደት ዝግጁነት" የሚለውን ቃል ሰምተህ ታውቃለህ? | 1. አዎ  2. አይደለም  3. አላስታውስም |  |
| 402 | በእርስዎ አስተያየት አንዲት ሴት ለመውለድ ለማዘጋጀት ምን ማድረግ ትችላለች? | 1) የመጓጓዣ ሁነታን መለየት,  1. አዎ 2. አይደለም   1. ገንዘብ ይቆጥቡ, 2. አዎ 2. አይደለም   3) ደም ለጋሾችን መለየት  1. አዎ 2. አይደለም  4) የሰለጠነ የወሊድ ረዳትን መለየት  1. አዎ 2. አይደለም   1. ደጋፊ ሰው   1. አዎ 2. አይደለም   1. ሌሎች ይግለጹ |  |
| 404 | የእርስዎ ማህበረሰብ ሴቶች ለመውለድ በሚዘጋጁበት ጊዜ ለመርዳት አገልግሎት ይሰጣል? ለምሳሌ፣ አሉ፡- | 1) የመጓጓዣ ሁነታን መለየት,  1. አዎ 2. አይደለም   1. ገንዘብ ይቆጥቡ, 2. አዎ 2. አይደለም   3) ደም ለጋሾችን መለየት  1. አዎ 2. አይደለም  4) የሰለጠነ የወሊድ ረዳትን መለየት  1. አዎ 2. አይደለም   1. ደጋፊ ሰው 2. አዎ 2. አይደለም 3. ሌሎች ይግለጹ |  |

ክፍል V በእርግዝና, በምጥ እና በወሊድ ጊዜ, አዲስ የተወለደ እና የድህረ ወሊድ ጊዜ አደገኛ ምልክቶችን ማወቅ

| **Sir. No.** | **ጥያቄዎች** | | **ምላሾች** | **Skip to** |
| --- | --- | --- | --- | --- |
| 501 | በእርስዎ አስተያየት ከእርግዝና ጋር የተያያዙ ያልተጠበቁ ችግሮች በማንኛውም እርግዝና ወይም ልጅ መውለድ የሴቶችን ሕይወት አደጋ ላይ ሊጥሉ ይችላሉ? | | 1. አዎ  2. አይደለም  3. አላስታውስም |  |
| 502 | በእርስዎ አስተያየት አንዳንድ ከባድ ችግሮች ምንድናቸው? | | 1. የደም መፍሰስ   1. አዎ 2. አይደለም   1. ከባድ ራስ ምታት   1. አዎ 2. አይደለም   1. የደበዘዘ እይታ   1. አዎ 2. አይደለም   1. መንቀጥቀጥ   1. አዎ 2. አይደለም   1. እብጠት እጆች / ፊት   1. አዎ 2. አይደለም   1. ከፍተኛ ትኩሳት   1. አዎ 2. አይደለም   1. የንቃተ ህሊና ማጣት   1. አዎ 2. አይደለም   1. የመተንፈስ ችግር   1. አዎ 2. አይደለም   1. ከባድ ድክመት   1. አዎ 2. አይደለም   1. ከባድ የሆድ ህመም   1. አዎ 2. አይደለም   1. የተፋጠነ / የተቀነሰ የፅንስ እንቅስቃሴ   1. አዎ 2. አይደለም   1. Water breaks without labor   1. አዎ 2. አይደለም   1. ሌሎች ይግለጹ 2. የለም 3. አላውቅም |  |
| 503 | በእርስዎ አስተያየት፣ ነፍሰ ጡር ሴትን ህይወት አደጋ ላይ የሚጥሉ ምጥ እና በወሊድ ወቅት ሊከሰቱ የሚችሉ ከባድ የጤና ችግሮች ምን ምን ናቸው?  PROBE: ሌላስ? | | 1. የደም መፍሰስ   1. አዎ 2. አይደለም   1. ከባድ ራስ ምታት   1. አዎ 2. አይደለም   1. መንቀጥቀጥ   1. አዎ 2. አይደለም   1. ከፍተኛ ትኩሳት   1. አዎ 2. አይደለም   1. የንቃተ ህሊና ማጣት   1. አዎ 2. አይደለም   1. Labor የሚቆይ>12 ሰዓታት   1. አዎ 2. አይደለም   1. Placenta ከተወለደ ከ 30 ደቂቃዎች በኋላ አልተወለደም   1. አዎ 2. አይደለም   1. ሌሎች ይግለጹ 2. የለም 3. አላውቅም |  |
| 504 | በእርስዎ አስተያየት አንዲት ሴት ከእነዚህ ችግሮች ውስጥ በአንዱ ልትሞት ትችላለች? | 1. አዎ 2. አይደለም 3. አላውቅም | |  |
| 505 | እንደ እርስዎ አስተያየት ከተወለዱ በኋላ ባሉት 2 ቀናት ውስጥ የሴቲቱን ህይወት አደጋ ላይ የሚጥሉ አንዳንድ ከባድ የጤና ችግሮች ምን ምን ናቸው?  PROBE: ሌላስ? | 1. አስቸጋሪ ወይም ፈጣን መተንፈስ   1. አዎ 2. አይደለም   1. ቢጫ የቆዳ/የአይን ቀለም (ጃንዲስ)   1. አዎ 2. አይደለም   1. ደካማ መጥባት ወይም መመገብ   1. አዎ 2. አይደለም   1. በእምብርት ገመድ አካባቢ የሚፈስ፣የደም መፍሰስ ወይም ፈሳሽ ፈሳሽ   1. አዎ 2. አይደለም   1. Baby በጣም ትንሽ   1. አዎ 2. አይደለም   1. የቆዳ ቁስሎች ወይም አረፋዎች   1. አዎ 2. አይደለም   1. መንቀጥቀጥ / spasms / ግትርነት   1. አዎ 2. አይደለም   1. ልቅነት / ንቃተ-ህሊና ማጣት   1. አዎ 2. አይደለም   1. ቀይ ወይም ያበጠ አይኖች መግል   1. አዎ 2. አይደለም   1. ሌሎች ይግለጹ_______ 2. የለም 3. አላውቅም | |  |
| **506** | በእርስዎ አስተያየት አዲስ የተወለደ ሕፃን ከእነዚህ ችግሮች በአንዱ ሊሞት ይችላል? | 1. አዎ 2. አይደለም 3. አላውቅም | |  |
| **507** | አዲስ ለተወለደ ሕፃን ወዲያውኑ ከተወለደ በኋላ ሊሰጡ የሚችሉ አንዳንድ መሠረታዊ እንክብካቤ ዓይነቶችን መጥቀስ ይችላሉ? | 1. ልዩ ጡት ማጥባት   1. አዎ 2. አይደለም   1. ደረቅ እና መጠቅለል 1. 1. አዎ 2. አይደለም 2. የአይን እንክብካቤ   1. አዎ 2. አይደለም   1. የገመድ እንክብካቤ 2. 1. አዎ 2. አይደለም 3. ሌሎች ይግለጹ_______ 4. አላውቅም | |  |

